#### Combined endocardial and epicardial group ablation

After obtaining pericardial access, a substrate map is constructed to identify abnormal electrograms. Activation mapping during VT – if possible – is done to prove epicardial involvement. Normal electrogram recordings show not more than three sharp and discrete deflections from baseline, amplitude >1.5 mV, duration <70 ms or amplitude-to-duration ratio >0.046 [9]. Before epicardial ablation, a coronary angiogram will be performed to avoid coronary artery damage. In addition to targeting abnormal potentials, epicardial homogenization will be performed. Ablation is continued until all abnormal potentials are gone.

### Clinical outcome and follow-up

Patients will be seen periodically up to 2 years (at 1, 3, 9, 12, and 24 months) after the index procedure. All implantable cardioverter defibrillator therapies and clinical events are reported.

The implantable cardioverter defibrillator will be programmed to detect VTs slower than the clinical VTs. Recommended implantable cardioverter defibrillator programming consists of a ventricular fibrillation zone with a cut-off rate of 220 beats per minute and a therapeutic VT zone with a cut-off cycle length of 60 ms below the slowest documented VT. To register VTs with rates below the detection limit, a monitor zone will be programmed with a cut-off rate of 120 beats per min. Detection duration will be 24/32 beats or 5 s in the ventricular fibrillation zone and 26 beats or 10 s in the therapeutic VT zone.

The analysis of recurrence of VT depends on the clear differentiation of VT from supraventricular tachycardia events. For reliable adjudication of arrhythmic events, implantable cardioverter defibrillator episodes with available electrograms are mandatory. In the case of single-chamber devices, the recommended setting is storage of both near-field and far-field (shock) electrogram sources. In addition, electrogram storage must be available before arrhythmia onset.

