## Methods/design

### Study design

The EPILOGUE study is a multicenter, two-armed, nonblinded, randomized controlled trial. Patients will be randomized to endocardial scar homogenization or endo-epicardial scar homogenization (Fig. 1). The study period is 2 years after the index procedure. All participating centers are tertiary referral centers for VT ablation with experience in epicardial ablation.

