### Primary and secondary outcomes

The primary outcome of this study is recurrence of sustained VT (defined as appropriate implantable cardioverter defibrillator therapy or VT >30 s duration) within 2 years. We will use a blanking period of 1 week after the ablation procedure. The secondary outcome parameters will be acute procedure success and procedure-related major complications. Procedural success will be defined as complete success if there is noninducibility of any sustained monomorphic VT. Partial success will be defined as noninducible clinical VT but inducible polymorphic VT, or VT with a cycle length <200 ms. Procedural failure will be defined as a spontaneous occurrence of VT or inducible clinical monomorphic VT.

Furthermore, the following data will also be determined: procedure time, fluoroscopy time, radiofrequency ablation time, time to recurrence of the ventricular arrhythmia, number of appropriate implantable cardioverter defibrillator therapies on follow-up, number of VT-related hospitalizations, freedom of antiarrhythmic drugs on follow-up, repeated (epicardial) ablation procedures, evidence of an incessant VT or VT storm during follow-up, and mortality.

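### The recommended ICD therapy-zone cut-off is worded in the wrong direction: a cycle length 60 ms shorter than that of the slowest VT is a faster rate, contrary to the stated aim

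*Protocol article*

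**What the plan says.** Clinical outcome and follow-up opens the device settings with an aim: "The implantable cardioverter defibrillator will be programmed to detect VTs slower than the clinical VTs". The settings follow:

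- VF zone: "Recommended implantable cardioverter defibrillator programming consists of a ventricular fibrillation zone with a cut-off rate of 220 beats per minute".
- Therapy zone: "a therapeutic VT zone with a cut-off cycle length of 60 ms below the slowest documented VT".
- Monitor zone: "To register VTs with rates below the detection limit, a monitor zone will be programmed with a cut-off rate of 120 beats per min".
- Detection time in the therapy zone: "26 beats or 10 s in the therapeutic VT zone".

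Primary and secondary outcomes ties device therapy to the endpoint. Recurrence of sustained VT is "defined as appropriate implantable cardioverter defibrillator therapy or VT >30 s duration", and the further data to be collected include the "number of appropriate implantable cardioverter defibrillator therapies on follow-up". No other section restates or corrects the therapy-zone cut-off.

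**The concern.** The aim calls for a therapy cut-off at a lower rate than the clinical VT, which means a longer cycle length. The setting, given in milliseconds of cycle length, goes the other way. A site that programmed what is printed would leave the patient's slowest known VT, and VTs somewhat faster than it, without device treatment.

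This also touches the endpoint. Appropriate ICD therapy is one of the two ways to become a primary event, so the therapy cut-off helps decide which episodes count. A treated VT counts whatever its duration. An untreated one counts only if it lasts more than 30 s. The count of appropriate therapies would also be lower.

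**Working it through.** **Inputs from the document.** 60 ms offset; VF cut-off 220 bpm; monitor cut-off 120 bpm; therapy-zone detection of 26 beats or 10 s; 30 s duration criterion. The document gives no VT rates, so the slowest-VT rates below are assumptions for illustration. It also gives no worked cut-off to reproduce, and the sample size calculation does not use this setting.

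**Conversion.** Rate (bpm) = 60000 / cycle length (ms). The VF cut-off is 60000/220 = 272.7 ms and the monitor cut-off is 60000/120 = 500 ms.

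**Direction.** With CL the cycle length of the slowest VT:

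- literal cut-off = 60000/(CL − 60), always faster than the slowest VT;
- intended cut-off = 60000/(CL + 60), always slower than it.

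The direction therefore does not depend on the assumed rates.

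**Band affected.** VTs from the intended cut-off up to the literal cut-off, or up to 220 bpm if that is lower, are treated under the intended rule and not under the literal one.

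| Slowest VT (assumed) | CL | Literal cut-off | Intended cut-off | Band (width) |
|---|---|---|---|---|
| 130 bpm | 461.5 ms | 401.5 ms = 149.4 bpm | 521.5 ms = 115.0 bpm | 115.0–149.4 (34.4) |
| 150 bpm | 400 ms | 340 ms = 176.5 bpm | 460 ms = 130.4 bpm | 130.4–176.5 (46.0) |
| 180 bpm | 333.3 ms | 273.3 ms = 219.5 bpm | 393.3 ms = 152.5 bpm | 152.5–219.5 (67.0) |
| 200 bpm | 300 ms | 240 ms = 250.0 bpm | 360 ms = 166.7 bpm | 166.7–220 (53.3) |

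**Upper end.** The literal cut-off reaches the VF limit when CL = 272.7 + 60 = 332.7 ms, a slowest VT of about 180 bpm. Above that rate the literal rule leaves no separate VT zone. A slowest VT at or above 220 bpm is treated in the VF zone under either reading.

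**Which episodes change event status.** Take a slowest VT of 150 bpm.

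- At the slow edge of the band, 26 beats take 26 × 0.460 = 11.96 s.
- At the fast edge, 26 beats take 26 × 0.340 = 8.84 s.
- The alternative criterion is a fixed 10 s.

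Only episodes in the band that last from about 9–12 s (beat criterion) or 10 s (time criterion) up to 30 s, and end by themselves, change from event to non-event. Longer ones count under both readings, provided they are recorded. The monitor zone records them from 120 bpm upward.

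**Lower end, after correction.** The intended cut-off equals 120 bpm when CL + 60 = 500, so CL = 440 ms and the slowest VT is 60000/440 = 136.4 bpm. At that cycle length or longer, the corrected therapy cut-off is at or below the fixed monitor cut-off. The monitor zone then has no slower VTs left to register. In the 130 bpm row the therapy cut-off is 115 bpm, and the 115–120 bpm part of the band lies below the monitor zone.

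**The case against.** The strongest reply is that the text corrects itself. The aim stands directly before the setting, the setting is only recommended, and the monitor-zone sentence uses the word below for rates. On that view the phrase loosely means a lower rate, with the margin in milliseconds. The literal rule also leaves no usable VT zone from about 180 bpm upward, which experienced staff would notice: "All participating centers are tertiary referral centers for VT ablation with experience in epicardial ablation". Finally, this is a condensed article, and the full protocol may be worded correctly.

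Much of this stands. The intent can be inferred, and what sites would actually program cannot be known from the article. It does not make the phrase right. The quantity is named as a cycle length, while the two neighbouring zones are given as rates, so the section itself separates the two scales.

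It might also be said that the 120 bpm monitor zone already meets the aim of detecting slower VTs. But that zone is described as covering VTs under the detection limit, so the limit in question is the therapy cut-off.

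Three stronger readings are tempting, and the document supports none of them:

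- **A bias between arms.** The programming is the same for both groups, and nothing shows that affected episodes would fall unevenly.
- **Recurrences missed wholesale.** VTs over 30 s at 120 bpm or faster still reach the endpoint through the monitor zone, and VTs faster than the literal cut-off are treated either way.
- **The slowest VT never treated.** This fails at or above 220 bpm.

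**Conclusion.** The cut-off is wrong as written, and the point is minor. The reversal follows from the inverse relation of rate and cycle length and needs no assumption about VT rates. Its size does: for assumed slowest VTs of 130 to 200 bpm, the affected band is about 34 to 67 bpm wide.

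The consequences are conditional on a site following the wording. They would then be untreated VTs within the band, the loss as primary events of self-terminating episodes between detection and 30 s, and a lower count of appropriate therapies. The share of episodes concerned cannot be derived from the document. The sample size is unaffected.

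**What to change.** Reword the setting, for both arms, as: *a therapeutic VT zone with a cut-off cycle length 60 ms longer than that of the slowest documented VT*.

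Add one sentence for slow VTs. Where the slowest VT has a cycle length of 440 ms or more (about 136 bpm or slower), so that the therapy cut-off is at or below 120 bpm, either set the monitor zone below the therapy cut-off or state that no separate monitor zone applies.

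The cost is one corrected phrase and one added sentence. No extra patients, visits or analyses are needed.

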### Adverse events

In compliance with medical ethics committee regulations, it is compulsory to register all serious adverse events. Death, acute myocardial infarction, coronary artery damage, type III and V major bleeding, abdominal bleeding, tamponade of more than 80 cm^3^, late tamponade, and an ischemic cerebral event are considered major adverse events. Dry right ventricle puncture, drainable hemopericardium, postprocedural precordial pain, phrenic nerve injury and type II minor bleeding [12] are considered minor adverse events.

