#### Pericardial access

In patients undergoing epicardial ablation, before ablation and systemic heparinization, subxiphoid pericardial access will be obtained by fluoroscopic guidance (lateral plane). Using a Tuohy needle, small amounts of contrast are injected while carrying out the puncture. Guided by fluoroscopy, a guide wire is inserted into the pericardial space and an Arrow sheath is placed. An appropriate sized guiding catheter is inserted to keep the sheath open. During ablation, we will use an irrigated tip catheter. The baseline flow should be reduced to 1 ml/min. Fluid will be drawn from the pericardial space frequently during the ablation.

At the discretion of the operator, epicardial phrenic nerve capture will be performed if the origin of the VT is located in the area of the phrenic nerve. When capture is performed, a balloon is inserted and inflated to avoid phrenic nerve damage during ablation.

At the end of the procedure, a pericardial drain is inserted for 24–48 h. The operator will administer an intrapericardial steroid injection. Colchicine should be prescribed for up to 1 month, commencing on the first day after the procedure. The first day post procedure Colchicine is dosed 1 mg twice daily followed by a maintenance dose of Colchicine 0.5 mg twice daily.

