### Safety of epicardial ablation

The reported complication rates associated with epicardial ablation range from 0.6 to 4.1 % [5, 6]. Procedure-related death in most studies was 0 % [5, 6, 16]. However, a study from Hamburg reported two procedure-related deaths in 59 patients undergoing epicardial VT ablations [14]. Thus, life-threatening complications might occur. Other reported major complications were [5, 6, 9, 16]:Hepatic bleeding;Pericardial bleeding requiring a drain;Phrenic nerve palsy;Pleuro-pericardial fistula;Coronary artery damage;Cardiac tamponade;Pericardial inflammatory reaction.

To prevent pericardial inflammation and subsequently adhesions, the use of colchicine after epicardial ablation is mandatory in our study [19].

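### The safety outcome counts major complications only, while two harms tied mainly to epicardial access are classed as minor and one bleeding class overlaps another

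*Protocol article*

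**What the plan says.** Under Primary and secondary outcomes, the protocol article sets the safety outcome: "The secondary outcome parameters will be acute procedure success and procedure-related major complications". The Adverse events section then divides events into two classes. Besides death, myocardial infarction and coronary artery damage, the major class is set by this wording: "type III and V major bleeding, abdominal bleeding, tamponade of more than 80 cm^3^, late tamponade, and an ischemic cerebral event are considered major adverse". The minor class is "Dry right ventricle puncture, drainable hemopericardium, postprocedural precordial pain, phrenic nerve injury and type II minor bleeding".

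The Discussion, under Safety of epicardial ablation, introduces a list taken from earlier studies with "Other reported major complications were". That list includes "Pericardial bleeding requiring a drain;Phrenic nerve palsy".

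On who is exposed, the Pericardial access section says: "In patients undergoing epicardial ablation, before ablation and systemic heparinization, subxiphoid pericardial access will be obtained by fluoroscopic guidance". The Study groups section rules out crossover at the first procedure.

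**The concern.** The trial asks whether adding epicardial ablation at the first procedure is worth its risk. The safety outcome is the part of the plan that measures that risk between arms, and it counts only what the article calls major. Two events that the article itself lists as major complications of epicardial ablation are minor when the trial counts its own events, and no reason is given for the difference.

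The two events are not spread evenly over the arms, because pericardial access at the index procedure belongs to the combined arm alone. A rule that drops them therefore acts mainly on one arm, in the direction that makes the tested strategy look safer. The boundary between the two pericardial-bleeding classes is also unclear, and the operator knows the assigned approach.

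**Working it through.** This is a check of definitions; the article gives no complication figure to reproduce.

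**1. The two events, section by section**

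| Event | Adverse events section | Discussion, Safety of epicardial ablation | Counted in the safety outcome? |
|---|---|---|---|
| Phrenic nerve injury or palsy | Minor | Among reported major complications | No |
| Hemopericardium that is drained | Minor if called drainable hemopericardium | Among reported major complications | Only if it also meets a major criterion |

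Phrenic nerve injury is the clearer case, because no item in the major list would catch it, however severe or lasting. A hemopericardium can still become major as a tamponade above 80 cm³, a late tamponade, or a type III or V bleed.

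**2. Which arm is affected**

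Pericardial access is described only for patients who have epicardial ablation. The phrenic nerve precaution appears only in that section: "a balloon is inserted and inflated to avoid phrenic nerve damage during ablation". At the index procedure both therefore concern the combined arm. The separation is not complete. Hemopericardium can also follow endocardial ablation, and the ablation protocol allows control patients a later epicardial redo.

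**3. The overlap**

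Take a pericardial bleed above 80 cm³ that is drained. It can be read as a tamponade of more than 80 cm³, which is major, or as a drainable hemopericardium, which is minor. The Adverse events section does not say which reading takes precedence. In the combined arm the line is harder still to draw: "Fluid will be drawn from the pericardial space frequently during the ablation", and a drain stays in for 24–48 h as routine. Drainage as such does not identify a complication there.

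**4. What a few events would do**

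- Sample size: the article's 86 patients can be reproduced. The hazard ratio is ln(0.85)/ln(0.56) = 0.280; Freedman's formula gives 25 events; 25/0.295 = 84.7, or 43 per arm. The stated total after dropout is 100. Assuming equal allocation, that is 50 per arm.
- Expected counts: the Discussion's range of 0.6 to 4.1 % gives 50 × 0.006 = 0.3 to 50 × 0.041 = 2.05 patients. The article calls these complication rates, not major-complication rates, so they show only that counts will be small.
- Effect on the reported rate: one recoded event is 1/50 = 2 percentage points, and two are 4 points.
- Effect on a test: with x events in one arm and none in the other, the two-sided Fisher p-value is 2 × C(50, x)/C(100, x). For x = 2 it is 2 × 1,225/4,950 = 0.49. For x = 5 it is 2 × 2,118,760/75,287,520 = 0.056. Even five events against none would miss the 5 % level.

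The frequency of phrenic nerve injury or drained hemopericardium in either arm appears nowhere in the article, so the resulting shift cannot be calculated.

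**The case against.** The strongest reply is that the Adverse events section is the trial's only operative definition. The Discussion list reports what earlier studies called major, and a trial may grade events differently from its sources. The terms also differ: phrenic nerve injury may be wider than palsy, and a drainable hemopericardium need not be a bleed that requires a drain. This stands in part. It makes the conflict one between the trial's classes and the severity label the article applies when it describes the known risk. It does not explain the difference, and it leaves the overlap at 80 cm³ untouched.

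A second reply is that the events are not lost. All serious adverse events must be registered, the clinical events committee studies them, and the data safety monitoring board may stop the trial for adverse effects in either arm. That is correct. The weakness lies in the between-arm outcome, not in detection.

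Four stronger readings are tempting, and the document does not support them:

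- **A reader might infer that epicardial harms as a whole are left out.** They are not. Coronary artery damage, abdominal bleeding, tamponade above 80 cm³, late tamponade and type III or V bleeding all count as major.
- **A reader might infer that the same bleed would be coded minor in the combined arm and major in the control arm.** The Adverse events section mentions neither arm nor route of drainage, and a control patient's hemopericardium can also be drainable. The ambiguity is in the text; a systematic difference by arm is conjecture.
- **A reader might put a figure on the understatement.** That needs arm-specific rates for the two events, which the article does not give.
- **A reader might object that pleuro-pericardial fistula and pericardial inflammatory reaction are in neither class.** A condensed article may leave such entries to the full protocol, so this is no defect.

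**Conclusion.** The point holds in limited form. As written, the safety outcome excludes phrenic nerve injury altogether and excludes drainable hemopericardium unless another major criterion is met. Both arise mainly in the combined arm, and the article elsewhere lists closely corresponding events as major. A drained bleed above 80 cm³ fits two classes, in a trial whose operators are not blinded.

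The direction follows from the design: some epicardial harm drops out of the comparison, in favour of the combined arm. The size cannot be derived. Assuming 50 patients per arm and low counts, recoding one or two events would change a reported rate by 2 to 4 percentage points and would be unlikely to alter a formal test. The primary outcome and the sample size are not affected. The conclusion assumes that palsy falls within phrenic nerve injury and that the two descriptions of drained pericardial bleeding overlap.

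**What to change.** Reconcile Primary and secondary outcomes, Adverse events and Safety of epicardial ablation in four steps:

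1. Define the two pericardial-bleeding classes so that each event falls into exactly one, and apply the same definition in both arms. A simple rule on volume drained, whatever the route, would not do. Irrigation fluid is aspirated and a drain is routine in the combined arm, so the rule could count fluid that is not blood in that arm only.
2. Classify phrenic nerve palsy in line with the Discussion, or state why the trial grades it differently.
3. Keep the major-only outcome, and beside it compare all procedure-related complications, major plus minor, by arm as randomised. The safety conclusion then no longer depends on where the line is drawn.
4. Settle the definitions before outcome data are compared by arm.

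The cost is some rewording of the outcome and adverse-event definitions, a matching change to the event form, and one further comparison. Sample size does not change. The downside for the sponsor is that the combined arm's complication rate may look slightly higher.

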### Safety monitoring

Two committees and one monitor will be appointed to monitor patient safety. A data safety monitoring board will review study progress and has the authority to end the study if significant benefits or adverse effects in either study arm are suspected. The board members are three experienced electrophysiologists and a statistician. The clinical events committee will study all serious adverse events for a causal relationship between events and the EPILOGUE study. A monitor will evaluate protocol compliance by taking random samples in all participating centers.

### Statistical analysis

Continuous variables between groups will be compared using Student’s *t* test or the Mann–Whitney test for continuous variables, where appropriate. Categorical variables between groups will be compared with the chi-square test or Fisher’s exact test, where appropriate. The primary outcome parameter will be analyzed using Kaplan–Meier survival curves and tested with a log-rank test. A two-sided *P* value of 0.05 will be considered statistically significant for all analyses. Statistical analysis will be performed using SPSS version 20.

### Sample size calculation

Sample size was calculated based on the following assumptions: a 29 % difference in primary outcome event rate (recurrence of VT) between the endocardial and epicardial group (15 %) and the control group (44 %) after a follow-up time of 2 years [9]. We calculate that a sample size of 86 patients is required to achieve an 80 % power to detect a significant difference with a (two-tailed) alpha error of 5 %. Allowing for a dropout rate of 10 %, we calculated that we would require 100 subjects.

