### Role of epicardial ablation

In 73 % of unsuccessful endocardial ablations, evidence of an epicardial substrate of VT was found [14]. To reach procedural success in VT ablation, Cesario et al. [15] found that 40 % of the patients were in need of an epicardial ablation. A recent retrospective observational study from Tung et al. [16] compared the outcomes of patients who underwent epicardial ablation with the outcomes of patients who did not. The pericardial space could not be accessed in 7 % by the percutaneous technique. The study demonstrated that at 12 months those with an ischemic substrate for VT who underwent a combined endocardial and epicardial ablation had improved freedom from VT compared with those who underwent endocardial-only ablation (85 % versus 56 %; *P* = 0.03). In a multicenter study by Della Bella et al. [5], 67 % of a subgroup of patients with ischemic VT etiology were in need of a stepwise approach. It could be speculated that an endocardial and epicardial approach as a first-choice ablation strategy in this subgroup might have avoided a substantial number of repeat procedures and improved outcome.

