### Epicardial ablation in ischemic cardiomyopathy

Multiple studies on epicardial VT ablation in scar-related VT have been published [5, 9, 15, 17, 18]; however, few have compared endocardial ablation with a combined endocardial and epicardial ablation.

In 33 post-infarct patients [17], epicardial mapping was performed when endocardial ablation failed. These 33 patients were retrospectively compared with patients who had had an endocardial ablation only. There was found to be no difference in outcome. However, only 6 % of the patients had had an epicardial ablation.

A recent study from Di Biase et al. [9] compared limited endocardial substrate ablation with combined endocardial and epicardial scar homogenization in patients with an electrical storm and ischemic cardiomyopathy. There was a lower VT recurrence rate in those who underwent endocardial and epicardial scar homogenization during a mean follow-up of 25 months (19 % versus 47 %; *P* = 0.006). A limitation of this study is that because these researchers used a historical control group, the technique of ablation (limited substrate ablation versus scar homogenization) differed between groups.

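### The sample size inputs (15 % v 44 % at 2 years) are attributed to [9], but the article reports [9] as 19 % v 47 %; 15/44 match the 12-month result of another study, [16]

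*Protocol article*

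**What the plan says.** All of the following is in the protocol article.

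- **Sample size calculation.** The effect is "a 29 % difference in primary outcome event rate (recurrence of VT"), split "between the endocardial and epicardial group (15 %) and the control group (44" %), "after a follow-up time of 2 years [9]". From this the article concludes that "a sample size of 86 patients is required to achieve an 80 % power" with "a (two-tailed) alpha error of 5" %. A 10 % dropout allowance takes the total to 100.
- **Epicardial ablation in ischemic cardiomyopathy (Discussion), on [9].** "There was a lower VT recurrence rate in those who underwent endocardial and epicardial scar homogenization during a mean follow-up of 25 months"; the figures given are 19 % versus 47 %. The same paragraph names as a limitation that, because of historical controls, "the technique of ablation (limited substrate ablation versus scar homogenization) differed between groups".
- **Role of epicardial ablation (Discussion), on [16], a retrospective observational study.** "The study demonstrated that at 12 months those with an ischemic substrate for VT who underwent a combined endocardial and epicardial ablation" had better freedom from VT than those with endocardial ablation only, 85 % versus 56 %.
- **Primary and secondary outcomes; Statistical analysis.** The primary outcome is recurrence within 2 years, tested with the log-rank test.

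**The concern.** The sample size section and the Discussion cannot both be describing [9]. They differ in both arms (15 against 19, 44 against 47). The only place that links 15/44 to [9] is the citation in the sample size section. The complements of the [16] figures match 15/44 in both arms, but those are 12-month figures, while this trial's horizon is 24 months.

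The assumed pair of rates is the sole basis for the number of patients. As written, a reader, an ethics committee or the monitoring board cannot tell which study, which rates or which follow-up time justify 100 patients, nor what power the trial has if the rates of the cited study apply.

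**Working it through.** **Inputs.** Two-sided alpha 0.05 and power 0.80 (z = 1.960 and 0.842), 15 % v 44 %, 86 before dropout: Sample size calculation. 19 % v 47 %: Discussion on [9]. 85 % v 56 % free of VT at 12 months: Discussion on [16]. The allocation ratio is not stated; 1:1 is assumed.

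**1. Does 86 follow from 15 % v 44 %?** Yes, by two standard routes.
- Freedman's log-rank formula: HR = ln(0.85)/ln(0.56) = 0.280. Events = (1.960 + 0.842)² × [(1 + 0.280)/(1 − 0.280)]² = 24.8. Mean event rate = (0.15 + 0.44)/2 = 0.295. N = 24.8/0.295 = 84.2; with 25 whole events, 25/0.295 = 84.7, so 86 in equal arms. Power at 86 is 80.8 %.
- Fisher's exact test by full enumeration: 79.4 % at 42 per arm, 80.5 % at 43 per arm, so 86.
- Dropout: 86/0.9 = 95.6, so 96; the stated 100 is rounded up. 100 × 0.9 = 90 evaluable.

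**2. Where do 15 and 44 come from?** 100 − 85 = 15 and 100 − 56 = 44. Both arms of [16] match exactly; neither arm of [9] matches.

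**3. The rates that the article gives for [9], 19 % v 47 %.**
- HR = ln(0.81)/ln(0.53) = 0.332; mean event rate 0.33; expected events in 86 patients = 86 × 0.33 = 28.4.
- Freedman: events needed = 2.802² × (1.332/0.668)² = 31.2, N = 31.2/0.33 = 94.5 (98 with 32 whole events and equal arms).
- Fisher: 79.7 % at 49 per arm, 80.8 % at 50 per arm, so 100.

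| Method, 19 % v 47 % | Power, 86 patients | Power, 90 patients | N for 80 % |
|---|---|---|---|
| Freedman log-rank | 76.2 % | 78.0 % | 95 to 98 |
| Fisher's exact | 74.4 % | 76.5 % | 100 |
| Chi-square, uncorrected | 79.9 % | 81.7 % | 88 |
| Log-rank, simulated (exponential times, censored at 2 years) | about 81 % | about 82 to 83 % | – |

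**4. 15 % v 44 % read as 12-month rates.** Under constant hazard (an assumption), 24-month recurrence is 1 − 0.85² = 27.8 % and 1 − 0.56² = 68.6 %. The HR is unchanged at 0.280, but events in 86 patients rise to 86 × (0.278 + 0.686)/2 = 41.4. Power at 86 is then 95.1 % (Freedman), 95.5 % (Fisher) and about 98 % (simulated log-rank).

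**The case against.** The strongest reply is that this is a citation slip with no effect on the design. Much of it stands. No arithmetic is wrong: 86 and 80 % follow from the stated rates. The planned test, simulated at the rates of [9], still has about 81 % power. A wrong horizon, taken alone, errs on the safe side. That 15/44 come from [16] is an inference, though a strong one. None of this removes the contradiction in the current text about the one assumption behind the sample size.

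Three stronger readings are tempting and not supported.

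- **That the trial is underpowered.** The power loss at 19/47 appears with Freedman and Fisher but not in the simulated log-rank test, and the 12-month reading points the other way.
- **That 86 was computed for Fisher's exact test although the log-rank test is planned.** Freedman's log-rank formula also leads to 86, and the article names no formula, so 86 cannot identify the method.
- **That scar homogenization in the control arm will lower its event rate and cut power sharply.** The article says that the controls in [9] had limited substrate ablation and that both groups here get homogenization, so the difference is real and disclosed. But it gives no rate for homogenized controls; a figure such as 35 % would be illustrative only. The article (Discussion, Study design) also says that only 14 of 43 patients in the combined group of [9] had epicardial ablation, so the rate in this trial's combined arm could differ too, possibly downwards.

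**Conclusion.** The point holds as an inconsistency of source and time horizon, not as a calculation error. The article attributes 15 % v 44 % at 2 years to [9], while its own account of [9] is 19 % v 47 % at a mean of 25 months; 15/44 very probably come from the 12-month result of [16]. Depending on which reading is correct and which method is used, the power of 86 patients runs from about 74 % (19/47, Fisher) to about 98 % (15/44 at 12 months carried to 24, simulated log-rank). This rests on 1:1 allocation, on exponential event times for the simulation, and on constant hazard for the 12-month reading. It should be corrected because the sample size rests on it alone, but it does not rank as a must-fix for underpowering.

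**What to change.** Rewrite the sample size paragraph so that it agrees with the Discussion.

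1. Choose one basis: either use 19 % v 47 % from [9], or cite [16] for 15 % v 44 % as 12-month rates and state how they are carried to 24 months.
2. Name the formula for the planned log-rank test and give the HR and expected events: HR 0.33 with about 90 × 0.33 = 30 events for 19/47, or HR 0.28 with about 90 × 0.482 = 43 events for 15/44 carried to 24 months under constant hazard.
3. Restate the power of the fixed 100 enrolled (90 evaluable) under the chosen rates. At 19/47 this is 78.0 % by Freedman and about 82 to 83 % by simulation.
4. Note beside the rates that the controls in [9] had limited substrate ablation while controls here get scar homogenization. Any lower control rate should be labelled as an illustrative sensitivity case.

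The cost is one reworded paragraph. It needs no added patients and no change of design or analysis; the stated power may become slightly less favourable if the rates of [9] are adopted.
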